# **Security analysis.** Lists of adverse events and serious adverse events will be provided by study group and a descriptive analysis will be performed in each group (ANNEX 1).

**Ethical aspects**

The study will be approved by the Research Ethics Committee with medicines from our Community. The corresponding Informed Consent will be obtained from the participants. The Standards of Good Clinical Practice, the current legislation regarding clinical trials (Royal Decree 1090/2015, of December 4, which regulates clinical trials with medicines, the Research Ethics Committees) will be complied with at all times with medicines and the Spanish Registry of Clinical Studies) and biomedical research (Law 14/2007, of July 3, on biomedical research). Timely authorization will be requested from the AEMPS as a clinical trial. The treatment, communication and transfer of personal data of all participants will comply with the provisions of the applicable regulations (Regulation (EU) 2016/679 of the European Parliament and of the Council, of April 27, 2016 on Data Protection (RGPD) and Organic Law 3/2018, of December 5, on the Protection of Personal Data and guarantee of digital rights. The promoter will request the classification of the clinical trial as a low level of intervention given that HDQ is is currently using SARS CoV2 infection treatment in clinical practice, in which case the institutional insurance policy will cover all possible damages that the patient may suffer as a result of the application of the studied procedure, in accordance with the Applicable legislation In the event that the trial is not considered to be of low level of intervention, the promoter will contract an insurance policy for this purpose, which will be reno periodically for the duration of the study.

Written informed consent will be obtained from the participants prior to their inclusion by a member of the research team.

The biological material of all patients will be treated in accordance with Law 14/2007 on Biomedical Research. The samples obtained from blood will be used for the measurement of conventional analytical parameters, inflammation markers and other laboratory parameters, as well as the serology of the viral infection. Two plasma samples will be taken throughout the project (baseline and at 10 weeks) of 5 ml each that will be stored in the BioBanco Valdecilla and can be used in research projects related to this pathology for which you will have to sign a consent specific informed. One of the samples will be stored for DNA. The monitoring of the aspects of drug safety surveillance: notification of serious adverse events from the researcher to the promoter and expedited notification of Serious and Unexpected Adverse Reactions to the Health Authorities, will be carried out following current regulations.

The competent authorities and the Ethics and Drug Research Committee may have access to the data from this trial.

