**TITLE:** Controlled, double-blind, randomized trial to assess the efficacy and safety of hydroxychloroquine chemoprophylaxis in SARS CoV2 infection in healthcare personnel in the hospital setting (SANsinCOVID).

**Promoter:** Instituto de Investigación Valdecilla (IDIVAL)

**Code:** SANsinCOVID

**EudraCT:** 2020-001704-42

**Main investigators:** [name]. Jefe Servicio Digestivo

[name]. Jefe Servicio Infecciosas

**Collaborating investigators:** [name]. Jefe Servicio Medicina Interna

[name]. Jefe Servicio Neumología

[name]. Jefe Servicio Preventiva.

[name]. Jefe S. Riesgo Laborales

[name]. Jefe Servicio Inmunología

[name]. Reumatología

[name]. Servicio Farmacia Hospitalaria

**Funding:** This study has no source of funding.

**Contact:** - Clinical Research and Clinical Trials Unit Marqués de Valdecilla University Hospital

- [name].

- Santander Tel .: [name] [contact]

- Email: [[contact]](mailto:[contact])

1. **Summary**

Health professionals have a high risk of SARS CoV2 infection as evidenced by the data observed in China, Italy and Spain (about 10,000 at the moment, 12-15% of all registered cases, data from the Ministry of Health). This risk is higher in professionals who work in high risk areas where aerosols can be produced. Hydroxychloroquine (HDQ) has been shown to inhibit coronavirus in vitro, although very little clinical results are available. HDQ is a widely used, low-cost, limited-toxicity drug. Currently, there is no type of exposure prophylaxis that has proven to be useful against SARS CoV2. For this reason, we intend to develop a randomized, double-blind, controlled clinical trial with two parallel groups (200 mg of HCQ per day versus placebo) with a prophylaxis duration of 60 days.

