**Dosage and safety of HDQ:** HDQ is a safe drug, in which one of the study researchers has extensive experience. Although it is common to perform a baseline eye exam to rule out maculopathy, the truth is that doses below 5 mg / kg are safe in almost all patients. In this sense, the risk of maculopathy is close to 1% after 5-7 years of treatment, which suggests that the risk in treatments of less than 6 months duration such as the one we are proposing is minimal or negligible. Factors that increase the risk of maculopathy include high doses (> 6mg / kg / day), prolonged exposure, the presence of kidney failure or previous maculopathy and the concomitant use of tamoxifen. Another relevant and relatively frequent side effect is skin rash, sometimes extensive. Cardiac arrhythmias have been described in patients with a prolonged QTc interval, so these subjects will be excluded from the study. Also, HDQ is safe during pregnancy. The only two chemoprophylaxis trials listed on clinicaltrails.gov use the 200 mg daily dose. There is no other evidence available. For this reason, the proposed dose is 200 mg daily in a single dose.

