**Secondary objectives.**

2) To assess the safety of HDQ for 2 months in healthcare personnel.

3) To evaluate the number of working days lost as a result of symptomatic or asymptomatic infection with COVID19.

4) To analyze the percentage of severe respiratory disease by COVID-19 in healthcare personnel.

5) To define the incidence, prevalence and severity of SARS CoV-2 infection in healthcare personnel in the hospital setting.

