**Methodology. Design, study subjects, variables, data collection and analysis, and study limitations.**

**Study design.** Prospective, randomized and placebo-controlled clinical Trial. The medication will be manufactured in the Pharmacy of the Marqués de Valdecilla University Hospital (HUMV). Two groups will be analyzed with a 1: 1 randomization. The allocation to both arms will be done through the generation of a sequence of random numbers by computer. Chemoprophylaxis group (n = 225): One 200 mg HDQ tablet once daily for two months. Control group (n = 225): One placebo tablet (identical to that of the drug) once a day for two months.

**Study population.** It will include 450 health professionals who are working in areas of high exposure and high risk of transmission of SARS CoV2 (professionals from the Hospital in COVID areas, Intensive Care Unit, Emergencies, Anesthesia and all those who carry out procedures that generate aerosols).

**Inclusion criteria:** 1) Health professional aged between 18 and 65 years (inclusive) at the time of the first screening visit. 2) They must provide signed written informed consent and agree to abide by the study protocol. 3) Active work in high exposure areas during the last two weeks and during the following weeks.

**Exclusion criteria:** 1) Previous infection with SARS CoV2 (positive coronavirus PCR or positive IgG serology with SARS Cov2 negative PCR and absence of symptoms). 2) Current treatment with HDQ or chloroquine. 3) Contraindication for taking HCQ (known epilepsy, porphyria, recent ischemic heart disease). 4) Previous or current treatment with tamoxifen or raloxifene. 5) Previous eye disease, especially maculopathy. 6) Known heart failure (Grade III to IV of the New York Heart Association classification) or prolonged QTc. 7) Any type of cancer (except basal cell) in the last 5 years. 6) Refusal to give informed consent. 8) Evidence of any other unstable or clinically significant untreated immunological, endocrine, hematological, gastrointestinal, neurological, neoplastic or psychiatric illness. 9) Antibodies positive for the human immunodeficiency virus. 10) Significant kidney or liver disease. Pregnancy or lactation; Hypersensitivity or allergy to HQ, cq contraindication in data sheet to taking HQ.

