**Questionnaire and variables to analyze.** Demographic data. Profession (assistant, technician, caretaker, nurse, doctor). Specialty and definition of the job. Follow-up of the recommendations (use of PPE, hand hygiene). Definition and history of the type of contact (s): 1) Close contact with possible, probable or confirmed case with required PPE use. 2) Close contact with possible, probable or confirmed case without use of required PPE. 3) Casual contact with possible, probable or confirmed case with the use of required PPE. Comorbidities (HT, DM, Smoker, Pulmonary, cardiac pathology). Pharmacological treatment at the time of inclusion in the study. Information about the COVID19 infection if it occurs (date of diagnosis). **Analytical evaluation:** Leukocyte count, platelets, hemoglobin, prothrombin activity, INR, urea, creatinine, glucose, cholesterol, HDL, LDL, AST, ALT, alkaline phosphatase, GGT, bilirubin, albumin, sodium, potassium, prothrombin rate, proteins totals, triglycerides, ferritin, uric acid, PCR. **Electrocardiogram. A sample for research** will be obtained at baseline and + 10 weeks, which will be transferred and stored in the Biobank for future research in the line of research; one of the samples will include DNA. **Clinical manifestations:** cough, odynophagia, fever, dyspnea, pleuritic pain, headache, diarrhea, anosmia, ageusia, others. **Severity:** qSOFA scale, CURB-65, evolution to ARDS, need for mechanical ventilation. Radiological manifestations. **Treatment** of the infection**. Evaluation of the adverse effects** of the administered medication**.**

**Main outcomes**The primary outcome of this study will be to evaluate:

Number and percentage of subjects presenting symptomatic and asymptomatic infection (see “Diagnosis of SARS CoV2 infection” below) by the SARS-Cov2 virus during the study observation period (8 weeks) in both treatment arms.

Number and percentage of subjects in each group presenting Pneumonia with severity criteria (Curb 65 ≥2) and number and percentage of subjects requiring admission to the Intensive Care Unit (ICU) in both treatment arms

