# **General considerations of statistical analysis.** The data will be analyzed using the SPSS version 21 program. A descriptive analysis will be performed at baseline and at the end of the follow-up (week 96) of the data using mean and standard deviation or median and range when necessary for quantitative data and percentage for qualitative data. The quantitative variables will be compared with t-student and the qualitative variables will be compared with X2. When the variables do not follow a normal distribution, non-parametric tests will be used. Prevalence, cumulative incidence, and incidence rate will be determined with their 95% confidence intervals by standard methods. Paired data tests will be used to analyze baseline results and end of treatment.

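### The safety analysis is a description within each group; no drug-minus-placebo estimate with an interval is planned (cheap improvement, minor)

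*Protocol*

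**What the plan says.** The title commits the trial to "assess the efficacy and safety of hydroxychloroquine chemoprophylaxis", and a secondary objective is "To assess the safety of HDQ for 2 months in healthcare personnel". The Study design paragraph describes a "Prospective, randomized and placebo-controlled clinical Trial" with 1:1 allocation and 225 per arm.

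The Security analysis paragraph holds the only text specific to how safety will be analysed, and it is a single sentence: "Lists of adverse events and serious adverse events will be provided by study group and a descriptive analysis will be performed in each group".

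Three other places bear on it:

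- Questionnaire and variables to analyze includes "Evaluation of the adverse effects" of the study medication.
- General considerations of statistical analysis states, without restricting it to efficacy, that "the qualitative variables will be compared with X2". It also states: "Prevalence, cumulative incidence, and incidence rate will be determined with their 95% confidence intervals by standard methods".
- Dosage and safety of HDQ names particular reactions. Besides arrhythmia in people with a prolonged QTc, it says: "Another relevant and relatively frequent side effect is skin rash, sometimes extensive".

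**The concern.** Annex 1 requires every adverse event to be recorded, whether or not it is caused by the study drug. Background complaints among working hospital staff will therefore enter both arms. The placebo arm is there to subtract that background, and what the trial can say about harm from the drug lies in the difference between arms. Two separate descriptions leave the reader to form that difference without any statement of its uncertainty.

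Two conclusions could then be drawn too easily. Percentages that look close, or a chi-square result that is not significant, could be reported as similar safety. A low count of serious events could be reported as absence of harm. The participants are uninfected workers taking a preventive drug, so the largest excess still compatible with the data is an important safety result.

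**Working it through.** The Protocol gives no safety figure to reproduce. The check has two parts: what each planned analysis delivers, and what the missing interval would show.

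**What the plan delivers for adverse events**

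| Source | Output | Size of the excess over placebo? | Interval for the excess? |
|---|---|---|---|
| Security analysis | Lists and description in each group | Only by subtracting the two percentages | No |
| General considerations, chi-square rule, if it covers safety | p-value | No | No |
| General considerations, 95% intervals, if they cover safety | Interval for an incidence in one group | No | No |

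**Inputs for the illustration**

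- Arm size: 225 per arm (Study design). Less the 5% dropout in the sample-size paragraph: 225 × 0.95 = 213.75, or about 214.
- Event rates: about 20% on drug and 15% on placebo. These are assumptions.

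**Chi-square, 43/214 against 32/214**

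The proportions are 0.2009 and 0.1495, a difference of 0.0514. The uncorrected statistic is 428 × (43 × 182 − 32 × 171)² / (214 × 214 × 75 × 353) = 1.96 on 1 degree of freedom, p = 0.16.

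**Newcombe 95% interval for the same data**

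Wilson limits in each arm:

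- Drug: 0.1527 to 0.2597
- Placebo: 0.1080 to 0.2035

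Lower limit = d − √[(p₁ − l₁)² + (u₂ − p₂)²] = 0.0514 − √(0.0482² + 0.0540²) = −0.021.

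Upper limit = d + √[(u₁ − p₁)² + (p₂ − l₂)²] = 0.0514 + √(0.0588² + 0.0415²) = 0.123.

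The difference is 5.1 points, 95% interval −2.1 to 12.3.

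**All 225 per arm**

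A set of everyone who took at least one tablet could be close to the full arm. With 45/225 against 34/225 the difference is 4.9 points, 95% interval −2.2 to 11.9. The choice of 214 or 225 hardly matters.

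**Range over assumed rates**

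Approximate half-width with the same rate p in both arms and 214 per arm: 1.96 × √[2p(1 − p)/214].

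| Assumed rate | Half-width (points) |
|---|---|
| 5% | 4.1 |
| 10% | 5.7 |
| 20% | 7.6 |

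**Power for an uncommon event**

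For 3% against 1% with 225 per arm, a two-sided 5% test has about 33% power. A non-significant chi-square result on such an event would say little.

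**The case against.** The strongest reply is that by-arm description of adverse events is common, that one sentence on it is a usual level of detail for a protocol, and that interval methods belong in a statistical analysis plan, which may exist and is not shown. Much of this stands. The choice of interval method and the list of event categories would not be a finding if the Protocol were merely silent. It is not silent: it states the safety analysis, and what it states is a description in each group. An analysis plan that followed it closely would have no between-arm estimate to specify.

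A reader might infer that the excess harm is never estimated and that safety is confined to lists. The documents do not support that. Results are given by group, so the crude difference can be read off. Adverse effects are among the variables to analyse, and the chi-square rule is not restricted to efficacy, so a comparison of proportions can be read in. The interval sentence is not restricted to infection either. None of these gives an interval for the difference.

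A reader might also infer that the Protocol promises safety against placebo. The main objective names placebo; the safety objective does not. The comparator comes from the design, so the description in each group does not contradict the objective.

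Two further points stand. Nothing is lost for good, because counts and denominators by arm allow the difference and its interval to be computed later. Naming a risk difference also does not improve precision. It only makes the imprecision visible. An upper limit for zero events in one arm (1.7% for 0 of 214, exact two-sided) would not answer the concern, since it bounds a rate in one group and not an excess over placebo.

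**Conclusion.** The point holds as a minor, inexpensive improvement. The stated safety analysis is within group, and even with the general rules read generously there is no between-arm estimate with an interval. The plan therefore does not say how large an excess over placebo the data still allow.

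In the illustration, a result that a test would call non-significant (p = 0.16) leaves an excess of about 12 points open. That figure rests on assumed event rates and on 214 to 225 per arm. At other rates the interval would be narrower or wider, as tabulated. The primary efficacy analysis is unaffected.

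**What to change.** In the Security analysis paragraph, keep the lists and the by-arm number and percentage, and add the hydroxychloroquine-minus-placebo risk difference with its 95% confidence interval (Newcombe or score method), in all participants who took at least one tablet, for:

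- any adverse event;
- events judged related;
- serious adverse events;
- events leading to stopping the tablets;
- the reactions the Protocol itself names (rash, arrhythmia).

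State in the same place whether the chi-square rule under General considerations applies to safety variables.

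The cost is one or two sentences and one extra table. Annex 1 already requires adverse events to be recorded at each assessment visit, so no further participants or visits are needed and clinical management does not change. The downside is that the intervals will be wide, especially relative to the rates of uncommon events, and the safety statement will be less reassuring than two percentages side by side.

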**Publication of results**

The researchers will disseminate the study results appropriately.

**ANNEXES**

**ANNEX 1. SIDE EFFECTS**

**SAFETY ASSESSMENT:**

**DEFINITIONS: ADVERSE EVENTS and ADVERSE REACTIONS**

Adverse Event (AA) is considered to be any adverse medical event that has occurred to a patient or a subject of the clinical investigation, although it does not necessarily have a causal relationship with the intervention of the investigation. An AA may also be any unfavorable or unexpected signs, including an abnormal laboratory finding, symptom, or disease temporarily associated with, or unrelated to, the investigational intervention.

Adverse Reaction (RA) is considered any harmful and unintended reaction to an investigational drug, regardless of the dose administered. Unlike an AA, in the case of RA, there is a suspected causal relationship between the investigational drug and the AA.

The recording of adverse events is an important aspect of the study documentation, therefore the rules to follow are described below:

**DETECTION AND DOCUMENTATION OF ADVERSE EVENTS**

It is the investigator's responsibility to document all adverse events (AA) that occur during the clinical trial.

At each visit / evaluation, all AAs observed (both by the researcher, by one of his clinical collaborators, and by those reported by the subject spontaneously or in response to a direct question), will be evaluated by the researcher and noted in the section AA from the subject data collection notebook.

AAs must be recorded at each assessment visit throughout the study. The nature of each event, the start time after the intervention, the duration, the severity and the relationship with the intervention must be established. The details of its management should be recorded on the corresponding pages of the data collection notebook. The initial symptoms should be well documented at the screening visit. It is important to correctly collect the baseline information to be able to interpret the data from subsequent visits.

AA follow-up: Investigators should follow AA subjects until they have decreased, disappeared, or until the process has stabilized. Reports regarding the course of the subject's course should be sent to the clinical trial monitor.

**ASSESSMENT OF CAUSATION or IMPUTABILITY**

The researcher must make every effort to explain each AA and assess its relationship, if any, with the procedure under study.

Based on all this, the promoter will classify the AA, based on their causal relationship with the drug, as:

- Definitive: there is a reasonable time sequence between the administration of the drug and the appearance of AA. This event coincides with the RA described for the drug, improves with its suppression, reappears after its re-administration and cannot be explained by alternative causes.

- Probable: there is a reasonable time sequence between the administration of the drug and the appearance of AA. This event coincides with the RA described for the drug, improves after treatment interruption and cannot be explained by other alternatives.

- Possible: there is a reasonable time sequence between the administration of the drug and the appearance of AA. This event coincides with the AR described for the drug, but can be explained by alternative causes.

- Conditional or Improbable: there is a reasonable time sequence between the administration of the drug and the appearance of AA. This event does not coincide with the AR described for the drug and can be explained by alternative causes.

- Unrelated: there is no reasonable time sequence between the administration of the drug and the appearance of AA. This event does not coincide with the AR described for the drug and can be explained by alternative causes.

For the purposes of expedited notification, the categories will be considered related: definitive, probable and possible; and as unrelated the conditional or improbable category.

The determination of the possible relationship with the study treatment is the responsibility of the main investigator of the research center or the person designated by it.

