**ASSESSMENT OF THE SEVERITY OF AN ADVERSE EVENT:**

Any adverse event or adverse reaction that, at any dose: will be considered serious.

- Cause the death of the patient

- Threatens the patient's life

- Require hospitalization or prolongation of hospitalization of the patient

- Causes permanent or significant disability or invalidity

- In place of a congenital anomaly or malformation

For the purposes of notification, suspicions of AA or RA that are considered medically important, even if they do not meet the above criteria, will also be treated as serious.

**Unexpected adverse reaction:** adverse reaction whose nature or severity does not correspond to the reference information.

The Principal Investigator will immediately report to the sponsor all serious adverse events. The initial communication will be followed by detailed written communications. In the initial and follow-up communications, the test subjects will be identified by means of a specific code number for each of them. In the event that a death has been reported to a subject participating in a clinical trial, the investigator will provide the promoter and the Clinical Research Ethics Committees involved with all the additional information requested.

The main investigator will communicate the serious and unexpected AAs to the promoter through the AAG form (Annex IV) by email to [contact] or fax to [name] within 24 hours after the investigator's knowledge of the AA. The previous report made by telephone or fax must be followed by a complete report that includes a copy of the relevant data collected or registered at the center or other documents that are produced as a consequence of the adverse event.

The promoter will notify the Spanish Agency for Medicines and Health Products (AEMPS) of all serious and at the same time unexpected suspicions of RA associated with investigational drugs. The maximum notification period will be 15 calendar days from the moment the promoter has become aware of the suspected adverse reaction.

When the suspicion of serious and unexpected adverse reaction has caused the death of the subject, or endangered his life, the promoter will inform the AEMPS within a maximum period of 7 calendar days from the moment the promoter becomes aware of the case. Said information must be completed, if possible, in the following 8 days.

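### The Annex 1 causality scale accepts only already-described reactions as related, which contradicts the protocol's duty to expedite suspected serious reactions of an unexpected nature

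*Protocol*

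**What the plan says.** All references are to the protocol; the main text is Annex 1.

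**Causality scale** (Assessment of causation or imputability). There are five categories. The first four require plausible timing. Beyond that:

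- Definitive: the event matches a reaction already described, resolves on withdrawal, returns on rechallenge and has no other explanation.
- Probable: "This event coincides with the RA described for the drug, improves after treatment interruption and cannot be explained by other alternatives".
- Possible: "This event coincides with the AR described for the drug, but can be explained by alternative causes".
- Conditional or improbable: "This event does not coincide with the AR described for the drug and can be explained by alternative causes".
- Unrelated: the same two conditions as improbable, but without plausible timing.

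The section uses both RA and AR; I read both as adverse reaction.

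**Reporting rule** (same section): "For the purposes of expedited notification, the categories will be considered related: definitive, probable and possible; and as unrelated the conditional or improbable category".

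**Definition of a reaction** (Definitions: adverse events and adverse reactions). What separates an adverse reaction from an adverse event is a suspected causal link to the investigational drug. Prior description is not part of the definition.

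**Definition of unexpected** (Assessment of the severity of an adverse event): "adverse reaction whose nature or severity does not correspond to the reference information".

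**Reporting duty** (same section, repeated under Notification and collection of serious adverse events). The promoter notifies the AEMPS of all suspected reactions that are both serious and unexpected, within 15 calendar days, or within 7 if the reaction is fatal or life-threatening.

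**Who decides.** The causality section first has the promoter classify each event. It ends differently: "The determination of the possible relationship with the study treatment is the responsibility of the main investigator", or that of a designee.

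**The concern.** Relatedness and expectedness are separate questions. Relatedness asks whether the drug may have caused the event. Expectedness asks whether the reference information already covers it. An expedited report of a serious unexpected reaction needs the answers yes and no, in that order. The Annex 1 scale builds part of the second question into the first: an event must already be described before it can be called related. A reaction of a new kind then has trouble passing the relatedness test for the very reason that makes it reportable.

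Safety is the first secondary objective. The participants are working health professionals, screened to exclude significant illness, who take a preventive drug. A rule that stands in the way of passing on a new serious reaction matters in that setting. With two parties named as deciding causality and no rule for disagreement, nothing ensures that one party's suspicion would override the scale.

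**Working it through.** The plan gives no figure to reproduce. The check is logical, and it can be made exhaustive.

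**Inputs.** The scale uses five yes/no criteria: plausible timing (T), already described for the drug (D), improves on withdrawal (W), reappears on re-administration (R), alternative cause available (A). They give 2^5 = 32 combinations.

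| Category | Conditions | Counts as related? |
|---|---|---|
| Definitive | T, D, W, R, not A | yes |
| Probable | T, D, W, not A | yes |
| Possible | T, D, A | yes |
| Improbable | T, not D, A | no |
| Unrelated | not T, not D, A | no |

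**Event already described (16 combinations).**

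- T, W, not A, with R free: 2 combinations, definitive or probable.
- T and A, with W and R free: 4 combinations, possible.
- Related in total: 2 + 4 = 6.
- T, not W, not A: 2 combinations, no category. A well-timed, described event with no other cause that does not improve, such as a fatal one, falls here.
- Not T: 8 combinations, no category, because unrelated requires an undescribed event.
- Sum: 6 + 2 + 8 = 16.

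**Event not described (16 combinations).**

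- T and A: 4, improbable.
- Not T and A: 4, unrelated.
- T and not A: 4, no category.
- Not T and not A: 4, no category.
- Related: 0. Sum: 4 + 4 + 8 = 16.

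All 6 related combinations have D = yes. These are counts of combinations, not frequencies of events, and some would be rare in practice. The result does not depend on how often each occurs, because D is a condition of every related category.

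**A single case traced through.** Take a serious event of an undescribed kind that follows dosing, resolves on withdrawal, returns on re-administration and has no other explanation. Definitive, probable and possible fail on D. Improbable and unrelated fail on A. The event has no category, although its profile is that of a genuine new reaction.

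**Side by side with the rest of Annex 1.**

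- The Definitions section would make this event an adverse reaction once a causal link is suspected. The scale will not call it related.
- If it is absent from the reference information it is unexpected in nature, so the promoter must notify it. The rule that states which categories are related for expedited notification does not let it through.
- A reaction of a described kind but unexpected severity has D = yes and can pass. The conflict is limited to reactions unexpected in nature.

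**The case against.** The strongest reply is that other text in the protocol points the other way, so one badly worded scale need not decide the outcome.

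- The investigator reports all serious adverse events to the promoter immediately, with 24 hours set for the form, and causality plays no part. Staff of the trials unit review each form. This stands: the promoter would hold the data, and the break can only come at the promoter-to-AEMPS step.
- The notification duty covers all suspected serious unexpected reactions, and Ethical aspects says safety surveillance follows current regulations. This also stands: the duty is present. A promoter could meet it, but only by setting the causality section aside.
- Described for the drug and the reference information are not defined as the same set. If described draws on a wider source, a reaction could be described, hence related, and still lie outside the reference information. This narrows the block to reactions described nowhere in that source. It does not remove the conflict with the Definitions section, which asks only for suspicion.

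A reader might go further and infer that new toxicity would drop out of the comparison between arms. The protocol does not support that. Security analysis plans lists of adverse and serious adverse events by study group with a descriptive analysis, and it does not filter them by causality. Annex 1 requires every adverse event to be documented. No listing restricted to related reactions is planned.

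**Conclusion.** The scale is wrong as written. It contradicts the definition of an adverse reaction and the notification duty in the same annex, and it is incomplete: 18 of the 32 combinations (2 + 8 described, 8 undescribed) have no category. None of the 16 undescribed combinations is classed as related.

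The practical consequence, that a serious reaction unexpected in nature cannot be classed as related for notification to the AEMPS, rests on two assumptions: that the causality section is followed literally, and that described means listed in the reference information.

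Two stronger readings are tempting. One is that such a reaction could never reach expedited reporting, or that the scale's sensitivity to it is zero. The notification duty elsewhere in Annex 1 contradicts this, and it also needs the second assumption. The other is that the scale labels the clearest new signal unrelated. It does not: an undescribed event with no alternative cause gets no label at all, since both improbable and unrelated require an alternative cause.

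Randomisation, the primary outcome and the sample size are not touched.

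**What to change.** Reconcile the causality section of Annex 1 with its Definitions, severity and notification sections:

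1. Remove prior description of the reaction as a precondition of definitive, probable and possible. Judge relatedness on timing, dechallenge, rechallenge and alternative causes.
2. Judge expectedness as a separate step, against a named reference document.
3. Give every event a category. Plausible timing with no alternative cause should be at least possible, whether or not the event is described and whether or not it improves.
4. Reconcile the two statements on who assigns causality, promoter or main investigator, and say what happens when they disagree. The protocol gives no rule for that case, so the sponsor must choose one.

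The cost is a rewording of Annex 1 and possibly some more expedited reports; the documents give no basis for a number. No visit, endpoint or sample size changes.
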